#### Secondary outcomes

In clinical routine, blood loss is measured gravimetrically by collecting the blood in canisters and weighing gauzes and absorbent drapes, including vaginal bleeding, up to 2 hours after CD. This outcome is also the source for the diagnostic codes O67.8 and O72.1 (Swedish version of the International Classification of Diseases, 10th edition, ICD-10). In accordance with the recommended core outcome set,^23^ five important measures of severe PPH are designated as secondary endpoints:

Gravimetrically estimated blood loss >1000 mL in the operating room or red blood cell transfusion within 48 hours after childbirth (binary).Total blood loss (in g) in the operating room (continuous).Red blood cell transfusion within 48 hours after childbirth (binary).Composite outcome of transfer to higher level care (intensive care or similar), prolonged stay in postoperative care >4 hours or prolonged postpartum hospital care >4 days (binary).Composite outcome of hypovolemic shock, hysterectomy, uterine tamponade, uterine artery ligation or embolisation treatment or other re-operation for internal or vaginal haemorrhage, surgical trauma to bladder, ureters or intestines, thromboembolism, organ failure, cardiac arrest or maternal death within 42 days (binary).

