### Sample size calculation

The primary outcome variable is the prevalence of calculated blood loss >1000 mL or red blood cell transfusion in the intervention group (external aortic compression) compared with the control group (no aortic compression). Around 12.4% of elective CDs have gravimetrically diagnosed PPH >1000 mL.^24^ To demonstrate a clinically relevant relative risk reduction of 30% at 80% power, n=1069 women in each treatment arm are needed, assuming a significance level of α=0.05, two-sided test. The sample size is inflated by 5% to account for drop-out and heterogeneity between centres, resulting in a total sample size of n=2246 women. This sample size is also sufficient to detect relatively rare outcomes, such as intensive care or hysterectomy. Sample size calculations were performed by using the POWER procedure in SAS/STAT Software, V.9.4 of the SAS System for Windows (SAS Institute Inc., Cary, North Carolina, USA).

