### Statistical analysis

Descriptive statistics will be used to characterise the groups recruited to the trial and to assess the comparability of the two groups at baseline. The primary efficacy analysis will be based on the intention-to-treat (ITT) population using a generalised linear mixed-effects model with log-link, Poisson distribution, treatment as a fixed effect and centre as a random effect to estimate the relative risk of event while accounting for centre effects. Similar methods will be employed for secondary and exploratory endpoints using appropriate models based on the type and distribution of the outcome. Patient-reported outcomes and questionnaire scales will be treated as numeric in this regard. Continuous variables will be adjusted for baseline values when applicable. All estimates will be provided with 95% CIs. Missing data exceeding 5% will be handled using multiple imputation.

The overall type-I error rate of the primary and five secondary endpoints will be retained at the 5% level using a hierarchical testing procedure. In case of a significant test for the primary endpoint, the entire probability mass will be transferred and distributed equally over the five secondary endpoints, that is, each receiving 1% of the total α=5%. The secondary endpoints will be tested sequentially, and the probability mass of a significant secondary outcome will be transferred (added) to the significance level for the next outcome in the order listed. All those significant tests will be considered confirmatory findings. Corrections for multiple testing of exploratory outcomes will be conducted using the Benjamini-Hochberg procedure, controlling the false discovery rate at the 5% level. Interaction analyses and subsequent subgroup analyses will be performed to assess treatment effects in subgroups and treatment effect heterogeneity based on having one or more risk factors for PPH with an OR of at least 3 in the literature: previous PPH, preeclampsia or multiple pregnancy.

Primary and secondary outcomes will also be presented for the per-protocol population. All safety outcomes will be presented for both the ITT population and the safety population (all randomised women according to actual treatment). The statistical analysis plan will be established in detail and signed before database lock and published as online supplemental material along with the main results.

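### The secondary-endpoint testing rule holds error at 5% but leaves alpha unused after the fifth endpoint; a return step would recover it at no cost in error control, for a small expected gain

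*Protocol article*

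**What the plan says.** The Statistical analysis section of the protocol article states the aim: "The overall type-I error rate of the primary and five secondary endpoints will be retained at the 5% level using a hierarchical testing procedure". The secondary endpoints are tested only after a significant primary: "In case of a significant test for the primary endpoint, the entire probability mass will be transferred and distributed equally over the five secondary endpoints", which gives each of them 1%. Among the secondary endpoints, "the probability mass of a significant secondary outcome will be transferred (added) to the significance level for the next outcome in the order listed".

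The Secondary outcomes section states that "five important measures of severe PPH are designated as secondary endpoints" and lists them in order:

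1. gravimetric loss above 1000 mL or red cell transfusion;
2. total blood loss in grams;
3. transfusion alone;
4. a composite of higher-level or prolonged care;
5. a composite of severe maternal events up to 42 days.

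The article describes no route from a later endpoint back to an earlier one and does not say what happens to alpha after the fifth. It leaves further detail to an SAP to be signed before database lock.

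**The concern.** The stated rule is a fallback procedure: 1% each, passed along the chain 1 → 2 → 3 → 4 → 5. Two consequences follow from the wording. Endpoint 5 has no next outcome, so its alpha is lost when it succeeds. Endpoint 1 has no predecessor, so it stays at 1% even if endpoints 2 to 5 all succeed.

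Endpoint 1 is not a minor endpoint. The Secondary outcomes section describes gravimetric measurement as the clinical routine and the source of the diagnostic codes, and the planning rate in Sample size calculation is a gravimetric one: "Around 12.4% of elective CDs have gravimetrically diagnosed PPH >1000 mL". At stake is whether an endpoint could miss confirmatory status only because alpha that was no longer protecting anything was left unused.

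**Working it through.** **The plan's own figures.** Five endpoints at 1% sum to 5%, as stated. For 12.4% against 0.7 × 12.4% = 8.68%, two-sided 5%, 80% power and pooled variance, n = (1.960 × √(2 × 0.1054 × 0.8946) + 0.842 × √(0.124 × 0.876 + 0.0868 × 0.9132))² / 0.0372² ≈ 1069 per arm. Then 1069 × 1.05 ≈ 1123 per arm, or 2246 in total. Both figures reproduce.

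**Alpha spent by the stated rule.** Under the closed-testing view, take any set of endpoints that are truly null and suppose that all others are rejected. Rejected endpoints pass their 1% forward to the next null endpoint. Alpha that lies beyond the last null endpoint has no recipient. The total spent on the set is therefore 1% × (position of its last endpoint).

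| Last null endpoint in the set | Number of sets | Spent, stated rule | Spent, with return |
|---|---|---|---|
| 1 | 1 | 1% | 5% |
| 2 | 2 | 2% | 5% |
| 3 | 4 | 3% | 5% |
| 4 | 8 | 4% | 5% |
| 5 | 16 | 5% | 5% |

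Of the 31 sets, 15 (1 + 2 + 4 + 8) spend less than 5%. These are exactly the sets without endpoint 5. With the return, the stranded alpha goes to the first null endpoint in the set, so every set spends exactly 5% and no endpoint has less than before. Family-wise error therefore stays at or below 5% under any dependence, and no rejection is lost. In simulation with endpoint 1 null and endpoints 2 to 5 strongly effective, the error was 1.0% under the stated rule and about 5.0% with the return.

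**Two worked examples.**

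- p = 0.03, 0.001, 0.001, 0.001, 0.001. Stated rule: endpoint 1 fails at 1%, and endpoints 2 to 5 pass at 1%, 2%, 3% and 4%. With the return, that 4% is added to endpoint 1's 1%, and 0.03 passes at 5%.
- p = 0.015, 0.001, 0.5, 0.2, 0.008. Stated rule: only endpoints 2 and 5 pass. With the return, endpoint 5's 1% brings endpoint 1 to 2%, and 0.015 passes.

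**Ceiling for endpoint 1.** Take 12.4% against 8.68%, 1123 per arm, and a Wald test on the log relative risk. SE = √(0.876 / (1123 × 0.124) + 0.9132 / (1123 × 0.0868)) = 0.125, and z = 0.357 / 0.125 = 2.85. Power is 61% at 1%, 75% at 3% and 81% at 5%. With 1069 per arm and the pooled test it is 58.9% at 1% and 80.0% at 5%. The 5% level is reached only if endpoints 2 to 5 all succeed.

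**Realistic gain.** The return acts only when endpoint 5 is significant and an earlier endpoint is not. At 1069 per arm and a 30% reduction, endpoint 5 has about 3%, 7% or 20% power at its own 1% for assumed control rates of 1%, 2% or 5%. The simulation below treats the secondary endpoints as independent of the primary result. It assumes control rates of 1% to 15% for endpoints 3 to 5, a 60 g difference with SD 350 g for endpoint 2, and uncorrelated endpoints.

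| Assumed endpoint 5 rate | Endpoint 1 power, stated → with return | Trials gaining an endpoint |
|---|---|---|
| 1% | 59.2% → 59.7% | about 0.5% |
| 2% | 59.3% → 60.5% | about 1.5% |
| 5% | 59.2% → 63.0% | about 5% |

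With correlation 0.5 the gains in endpoint 1 power are smaller: 0.2, 0.6 and 2.6 points.

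A patient-level simulation also kept the overlap between the primary and the secondary endpoints (assumed lognormal loss, transfusion 2%, endpoint 4 at 10%, 4,000 trials per setting). Given a significant primary, endpoint 1 already passed at 1% in 72% to 73% of trials. The return added 0.2 to 1.3 points, and 0.3% to 2.1% of such trials gained an endpoint. In the simulations that compared it, the chance of at least one significant secondary endpoint did not change.

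**The case against.** The strongest reply is that nothing here is wrong. The section promises a 5% family-wise rate and the rule delivers it; it does not promise to use every part of the alpha. A single pass in a fixed order is a legitimate design, and the loss after endpoint 5 is inferred from the words about the next outcome, not stated. The SAP could still complete the rule. The gain also depends on a composite of severe events that is probably rare, and the article's strengths and limitations box says that the trial is not powered for rare outcomes. Finally, changing a published multiplicity rule late in an open-label trial that has enrolled since December 2022 needs justification.

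Most of this stands. It settles that this is an efficiency point of low priority. It does not make the choice a matter of taste, because the usual trade between endpoints is absent: the looped rule is at least as good for every endpoint in every configuration.

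A reader might infer three stronger claims, and the documents support none of them:

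- That the type I error claim fails. It does not; the largest alpha spent on any set is 5.0%.
- That endpoint 1 loses about 20 points of power, from 61% to 81%. The upper figure is a ceiling that needs all four other endpoints to succeed.
- That 8% to 9% of trials would gain an endpoint. That needs an endpoint 5 effect such as 5% against 3%, a 40% reduction, where the article plans for 30%. A gain of 14% to 17% would need all five endpoints to have 80% power at the 5% level.

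**Conclusion.** The rule is valid, but another rule that is never worse is available. Alpha is left unused in 15 of the 31 possible null configurations, and the return step recovers it with family-wise error still at or below 5%. That part is exact and rests on no assumed rate. It does rest on reading the text literally (forward transfer only) and on reading the 1% for each endpoint as allowing testing to continue past a non-significant one.

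The size is modest: about 0.3% to 5% of trials with a significant primary would gain a confirmed endpoint, and endpoint 1 power would rise by about 0.2 to 4 points. These figures assume a 30% reduction and endpoint 5 control rates of 1% to 5%, with the other assumptions given in the working. The primary analysis, the estimates and the confidence intervals are unaffected. This is a free improvement of optional priority.

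**What to change.** In the Statistical analysis section or the SAP, state that the alpha of a rejected secondary endpoint passes to the next endpoint not yet rejected in the listed order, that after endpoint 5 it returns to the first endpoint not yet rejected, and that testing repeats until nothing more can be rejected. Keep the order, the 1% starting levels and the condition on the primary as they are. The guarantee that no rejection is lost holds for a return added at the end of the unchanged chain; other reroutings could lower power for later endpoints.

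The cost is one sentence and a documented amendment with its reason, made before database lock and without sight of unblinded data. It needs no further patients or data.

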#### Adverse events

Adverse events are defined as medical events other than outcomes and are classified as serious or not. Adverse events are assessed from medical records up to 42 days postpartum and reported by patients 6–8 weeks postpartum in an electronic survey and at the follow-up visit 6 to 12 months after delivery.

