#### Exploratory outcomes

##### Blood loss

B-Hb on day 1, 2 or 3 after childbirth (first value, continuous).B-EVF on day 1, 2 or 3 after childbirth (first value, continuous).Anaemia diagnosed within 7 days postpartum (diagnostic codes or B-Hb<100 g/L at any day before discharge) (binary).

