##### Morbidity (including use of resources)

Analgesic treatment in addition to regional anaesthesia during surgery or conversion to general anaesthesia (binary).Pharmacological treatment for low blood pressure (other than preventive) during surgery (phenylephrine, ephedrine, norepinephrine, intravenous crystalloid fluids) (binary).Use of additional uterotonic drugs (>16.6 µg oxytocin) (binary).Use of haemostatic drugs (eg, tranexamic acid) (binary).Use of intravenous iron replacement therapy (ferric carboxymaltose) (binary).S-creatinine on day 1, 2 or 3 after childbirth (continuous).eGFR on day 1, 2 or 3 after childbirth (continuous).Start-to-finish (incision to closure) surgery duration (min) (continuous).Days in postnatal care (mother) from the operation finish time to discharge (continuous).

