##### Patient well-being, satisfaction and acceptability

Intraoperative pain (NRS 0–10).Intraoperative breathing discomfort (NRS 0–10).Intraoperative nausea (NRS 0–10).Intraoperative overall experience (NRS 0–10).Edinburgh Postnatal Depression Scale^21^ at 6 to 8 weeks postpartum.Breastfeeding Self-Efficacy Scale short form^22^ at 6 to 8 weeks postpartum.Self-reported breastfeeding 6- to 12-week postpartum (retrieved from Swedish Pregnancy Register).Self-rated health 6- to 12-week postpartum (Likert scale 0–5, retrieved from the Swedish Pregnancy Register)

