##### Neonatal outcomes

Apgar score at 5 min <7 (binary).Apgar score at 10 min <6 (binary).Neonatal acidosis (cord vein or artery pH <7.0 or base deficit −16.0 mmol/L) (binary).Neonatal resuscitation or ventilatory support (binary).Admission to neonatal care (binary) 0–7 days.Neonatal hyperbilirubinaemia (binary) 0–7 days.Neonatal anaemia (binary) 0–7 days.Time to cord clamping (minutes, continuous).Severe neonatal adverse event composite outcome (hypothermic treatment, hypoxic ischaemic encephalopathy grade 2–3 or neonatal death within 28 days) (binary).

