### Data and safety monitoring

A data and safety monitoring board (DSMB) has been appointed, consisting of a statistician, an obstetrician and a gynaecologist, all independent of the study investigators and the funder. The DSMB will oversee participant safety, study conduct and data integrity throughout the trial. The board will review adverse events and study progress at predefined intervals (at 1000 included patients and once per year) and may recommend continuing, modifying or terminating the trial based on safety considerations or emerging evidence. The DSMB operates under a separate predefined charter that outlines its roles, responsibilities and decision-making procedures.

Study monitoring will be conducted in accordance with ICH GCP using a risk-based monitoring approach. Independent monitors will perform site initiation, interim and close-out visits, either on-site or remotely. Early source data verification will be performed for the first enrolled participants at each site, followed by source data verification of a random sample of approximately 10% of participants. Monitoring includes review of informed consent, eligibility criteria, protocol adherence, primary outcome data, adverse events, eCRF completeness and essential trial documentation. Additional monitoring may be undertaken if protocol deviations or data quality concerns are identified.

Trial participants are covered by the standard Swedish patient insurance system. Any necessary medical care related to pregnancy, childbirth or trial participation will be provided within the publicly funded Swedish healthcare system, where maternity and postpartum care is free of charge.

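### The outcomes that measure the protocol's own named harms fall under the false-discovery correction for exploratory outcomes, and the wording on adverse events leaves open whether the DSMB receives them

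*Protocol article*

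**What the plan says.** All places are in the protocol article.

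- **Statistical analysis.** The rule for exploratory outcomes is: "Corrections for multiple testing of exploratory outcomes will be conducted using the Benjamini-Hochberg procedure, controlling the false discovery rate at the 5% level". No outcome is exempted. The same section promises 95% CIs for all estimates. It also says that safety outcomes will be shown for the ITT population and for a safety population defined by treatment received, but the article never lists which outcomes these are.
- **Exploratory outcomes.** Kidney function is under Morbidity: "S-creatinine on day 1, 2 or 3 after childbirth (continuous).eGFR on day 1, 2 or 3 after childbirth (continuous". Discomfort is under Patient well-being, satisfaction and acceptability: "Intraoperative pain (NRS 0–10).Intraoperative breathing discomfort (NRS 0–10).Intraoperative nausea (NRS 0–10". Neonatal Outcomes includes "Neonatal acidosis (cord vein or artery pH <7.0 or base deficit −16.0 mmol/L) (binary", Apgar scores, resuscitation, admission to neonatal care and a "Severe neonatal adverse event composite outcome".
- **Secondary outcomes.** The fifth endpoint is a composite that holds the severe maternal harms, such as surgical trauma, thromboembolism, organ failure and death, together with haemorrhage-related events.
- **Adverse events.** "Adverse events are defined as medical events other than outcomes and are classified as serious or not".
- **Data and safety monitoring.** "The board will review adverse events and study progress at predefined intervals", namely at 1000 patients and yearly. The board also has a general remit over participant safety and works under a separate charter.
- **Discussion.** Three possible harms are named: impaired cord oxygenation and neonatal transition, kidney ischaemia, and unacceptable discomfort.

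**The concern.** Multiplicity control guards against false positive claims. Applied to harms, it makes a true harm less likely to be declared. Here the harms share the correction with measures such as iron therapy, surgery duration and breastfeeding. Whether a neonatal signal is flagged would then depend partly on how many unrelated outcomes reach significance.

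Compression is preventive and is given to every woman allocated to it, and safety and acceptability are among the stated secondary objectives. An adjusted, non-significant result on acidosis or creatinine could be taken as reassurance that the data do not give.

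The oversight wording adds a second difficulty. If an adverse event is by definition not an outcome, and the board's stated material is adverse events and progress, then the harms most carefully measured are the ones that the stated review does not mention.

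**Working it through.** **1. The plan's own figure.** Control rate 12.4%, relative reduction 30%, so 0.124 against 0.0868 (mean 0.1054, difference 0.0372); two-sided α = 0.05, power 80%.

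n per arm = [1.960·√(2·0.1054·0.8946) + 0.842·√(0.124·0.876 + 0.0868·0.9132)]² / 0.0372² = 1069 after rounding up, as stated. Then 1069 × 1.05 = 1122.45, rounded up to 1123 per arm, or 2246 in total, as stated. The article gives no power for any harm outcome. The steps below use 1123 per arm.

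**2. Number of exploratory items.** Blood loss 3, morbidity 9, well-being 8, neonatal 9, long-term 2: 3 + 9 + 8 + 9 + 2 = 31. This is a minimum, because both long-term items have several components.

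**3. Benjamini-Hochberg thresholds.** With k rejections among 31 tests, the threshold is 0.05·k/31.

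| Rejections k | Threshold |
|---|---|
| 1 | 0.0016 |
| 5 | 0.0081 |
| 10 | 0.0161 |

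The first step corresponds to |z| = 3.15 instead of 1.96.

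**4. Detectable difference.** The standardised difference detectable with 80% power is (z for α + 0.842)·√(2/1123).

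- α = 0.05: (1.960 + 0.842) × 0.0422 = 0.118
- α = 0.0016: (3.154 + 0.842) × 0.0422 = 0.169

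The squared ratio is 2.03: a lone signal at the first step needs about twice the sample size for the same power.

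**5. Power for a binary harm.** The rates are assumed for illustration; the documents give none.

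| Harm rates | Power at 0.05 | Power at 0.0016 |
|---|---|---|
| 2% vs 4% | 79% | 35% |
| 5% vs 7.5% | 69% | 24% |
| 10% vs 14% | 83% | 41% |

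**6. Allowing for the adaptive threshold.** Simulation of 31 independent tests, 40,000 runs. One harm has 80% power at 0.05; the other true effects have a mean z of 4.

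| Other true effects | Harm flagged |
|---|---|
| 0 | 37% |
| 5 | 58% |
| 10 | 67% |

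**7. A rare event.** Two-sided Fisher's exact test, k against 0 events: 6 vs 0 gives p = 0.031, 10 vs 0 gives 0.0019, 11 vs 0 gives 0.00095. A lone signal therefore needs 11 vs 0 to pass 0.0016. This is an illustration, not the planned model. It also counts one child per woman, although multiple pregnancies are eligible.

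**8. Dependence on the family.** The article does not say how the exploratory outcomes are grouped. Without the two long-term items the first step is 0.05/29 = 0.0017, hardly different. If each subheading were its own family, the first neonatal step would be 0.05/9 = 0.0056, and 9 vs 0 (p = 0.0038) would pass.

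**9. The oversight passages side by side.** Adverse events section: outcomes are excluded. Data and safety monitoring section: the board reviews adverse events and progress. Acidosis, encephalopathy, neonatal death, creatinine, thromboembolism, organ failure and maternal death are all listed as outcomes or as parts of outcomes. Read literally, they fall outside the stated review. The board's general safety remit, in the same section, points the other way.

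**The case against.** The strongest reply has five parts.

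- **The correction hides nothing.** Estimates and 95% CIs are promised throughout, and safety outcomes are to be shown in two populations. This stands. A reader might infer that harm data would be concealed; the article does not support that. What changes is whether a harm is declared.
- **Not all harms are exploratory.** This stands. Severe maternal harms are in the fifth secondary endpoint. That placement has its own limits, since they are mixed with haemorrhage events and tested confirmatorily only after a significant primary result, but the false-discovery correction does not reach them.
- **0.0016 is the worst case.** This stands. If compression works, related outcomes such as Hb, EVF and anaemia may also be rejected and raise the threshold. The loss shrinks but remains: 67% against 80% with ten strong effects.
- **The DSMB may well see these outcomes.** It has a safety remit and a charter that is not shown. The trial also compared cord gases, kidney function and discomfort between groups after 149 women, although the article does not say that the board received this. A reader might infer that the board is denied these data; the wording shows only an ambiguity.
- **A single family is inferred.** A reader might conclude that the correction cannot be completed until the 5-year register data arrive. The article does not say that those outcomes are pooled with the perioperative ones, and such grouping is usual SAP content. This calls for clarification and is not an error.

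The reply does not remove the central fact: the stated rule covers exploratory outcomes without exception, and the named harms are among them. The sentence on safety outcomes would help only if it said which outcomes it means and whether the correction applies to them.

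**Conclusion.** The point holds in limited form and should be acted on. The article's rule raises the bar for flagging neonatal, renal and discomfort harms, from 0.05 to between 0.0016 (lone signal) and about 0.016 (ten rejections). In the simulated cases, a harm with 80% nominal power is flagged 37% to 67% of the time. These figures assume one family of 31 and, for the percentages, independent tests and strong other effects; smaller families would soften them. The assumed harm rates are illustrative only.

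The DSMB part is a conflict of wording to be reconciled, for maternal and neonatal outcomes alike. It is not evidence that the board lacks the data.

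**What to change.** 1. List the safety outcomes to which the Statistical analysis section refers, from data already collected: the fifth secondary endpoint, creatinine and eGFR, the neonatal outcomes, and intraoperative pain and breathing discomfort.
2. Exempt the exploratory members of that list from the Benjamini-Hochberg correction and report unadjusted estimates with 95% CIs. The fifth secondary endpoint keeps its place in the testing hierarchy.
3. State in the protocol and charter that the DSMB receives this set by arm at each review, in addition to adverse events.
4. As a clarification only, state that the 5-year register outcomes form a separate family.

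The cost is wording in the protocol, SAP and charter, plus one DSMB table. The SAP is to be signed before database lock, so it can still carry the change. The downside is more chance signals: the exempted items number 2 + 9 + 2 = 13, so with no true effects about 13 × 0.05 = 0.65 would fall below 0.05, in either direction. The report should say that these are to be read as such.

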### Intervention

The effect of routine external aortic compression versus no aortic compression (standard care) in elective CD will be studied. Immediately after the surgeon has delivered the baby, but before placental delivery, the assistant surgeon applies external aortic compression by placing a fist onto the aorta through the abdominal wall at the level of the umbilicus. The aorta is compressed until bleeding is controlled, usually until the first layer of the hysterotomy is closed (figure 2). The surgeon may interrupt aortic compression or apply aortic compression in patients allocated to no aortic compression if deemed necessary, for example, when blood loss has visually exceeded 1000 mL.

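### The as-treated safety population pools control women given compression because they were already bleeding with women given routine compression, which biases bleeding-sensitive safety outcomes in that analysis

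*Protocol article*

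**What the plan says.** Three statements in the Protocol article bear on this point.

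- **Intervention.** Besides interrupting compression in the intervention arm, the surgeon may "apply aortic compression in patients allocated to no aortic compression if deemed necessary, for example, when blood loss has visually exceeded 1000 mL". Bleeding is thus the article's own example of why a control woman would be compressed.
- **Statistical analysis, safety.** "All safety outcomes will be presented for both the ITT population and the safety population (all randomised women according to actual treatment"). No exception is made for compression given as rescue.
- **Statistical analysis, efficacy.** The primary analysis is ITT. "Primary and secondary outcomes will also be presented for the per-protocol population", but the article does not define that population.

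The section on the procedure immediately after delivery says that compression duration and deviations from protocol are noted. It does not say whether permitted rescue counts as a deviation. The analysis plan is not shown; it is to be signed before database lock.

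**The concern.** Among control women, receiving compression is a consequence of heavy bleeding after randomisation. Grouping by treatment received therefore selects the control women with the worst bleeding and transfers them, with complications that may have begun before anyone compressed the aorta, to the compression side. The group left without compression is correspondingly depleted of such women. The regrouping alone creates an apparent harm, even if compression does nothing.

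Safety is a stated secondary objective, and the Discussion names impaired kidney circulation as one of the harms raised during planning. Creatinine and eGFR are measured after surgery. If heavy bleeding itself worsens them, rescued controls would add to an apparent renal signal for compression. Shock, re-operation and transfer to higher-level care would be exposed in the same way if they are analysed as safety outcomes. The trial could then publish two safety tables that disagree, with nothing in the article saying which one leads.

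**Working it through.** **Step 1: the plan's own figures.** Inputs from Sample size calculation: a control rate of 12.4%, a relative reduction of 30%, power of 80% and a two-sided α of 0.05. The treated rate is 0.124 × 0.70 = 0.0868. The two-proportion formula with pooled variance and no continuity correction gives 1069 per arm, as stated. Then 1069 × 1.05 = 1122.45, rounded up to 1123 per arm, and 2 × 1123 = 2246, also as stated. The arm size used below is therefore 1123.

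**Step 2: effect of the grouping rule on a harm with no true difference.** Let

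- p = risk of the harm, the same in both arms;
- x = share of the control arm given rescue compression;
- s = share of control-arm events that fall in those rescued women.

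Moving the rescued women to the compression side gives

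- compression rate = p(1 + s) / (1 + x);
- no-compression rate = p(1 − s) / (1 − x);
- as-treated RR = [(1 + s)(1 − x)] / [(1 − s)(1 + x)].

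The risk p cancels. The RR exceeds 1 whenever s > x, that is, whenever rescued women carry more than their proportionate share of the events. That is expected for an outcome that responds to bleeding when bleeding is the reason for rescue.

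**Step 3: numbers.** The article gives neither x nor s, so both are assumed. The values of x are 10%, 25% and 50% of the planned 12.4% of control women with severe bleeding: 0.0124, 0.031 and 0.062, or about 14, 35 and 70 women of 1123.

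| s | x = 0.0124 | x = 0.031 | x = 0.062 |
|---|---|---|---|
| 0.10 | 1.19 | 1.15 | 1.08 |
| 0.25 | 1.63 | 1.57 | 1.47 |
| 0.50 | 2.93 | 2.82 | 2.65 |

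The true RR is 1.00 in every cell. One cell in full, with an assumed p of 2%: there are 0.02 × 1123 = 22.46 events per arm. With s = 0.25, 5.615 events move, along with 34.8 women. Compression: 28.075 / 1157.8 = 2.42%. No compression: 16.845 / 1088.2 = 1.55%. RR = 1.57.

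**Step 4: removing rescued controls instead of moving them.** The RR against the remaining controls is (1 − x) / (1 − s). Over the same values of x this is 1.25 to 1.32 for s = 0.25 and 1.88 to 1.98 for s = 0.50. Exclusion is less distorting than transfer, but it does not remove the bias.

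**Step 5: by randomised arm.** Nobody moves, so the RR stays at 1.00 whatever x and s are.

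**The case against.** The strongest reply is that the randomised comparison is already there. The same sentence presents every safety outcome by ITT, the primary efficacy analysis is ITT, and the hierarchical testing covers only the primary and five secondary endpoints. No confirmatory result rests on the as-treated set. This stands and limits the point to a supplementary safety table. It does not remove the point, because that table would still be biased in a known direction and the article names no lead analysis.

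Second, safety outcomes are not listed. Adverse events are defined as events other than outcomes, and shock, re-operation and higher-level care are components of secondary endpoints. This also stands: for those events the concern is conditional on their being analysed as safety outcomes.

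Third, a treatment-received view has a use, since it shows harms in women who were actually compressed. A safety set by allocated arm alone would nearly duplicate ITT, because randomisation takes place in the operating room just before surgery. The view should therefore be kept, with rescued controls separated.

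Three stronger readings are tempting but not supported.

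- *The rule would reverse the haemorrhage result.* Applied to the planned 12.4% versus 8.68%, and assuming every rescued woman is an event, moving about 17% of control bleeders (about 23 of 139) would bring RR 0.70 to 1, and moving 50% would give 2.12. At 10% the RR is 0.87, with no reversal. More importantly, severe haemorrhage is the primary outcome, and the article does not assign it to the as-treated set.
- *The per-protocol comparison is reversed too.* The as-treated rule moves nobody in a per-protocol analysis. That set is undefined here, its definition may properly sit in the analysis plan, and expressly permitted rescue need not be a deviation. If rescued controls stay in, there is no such bias; if they were excluded, reversing RR 0.70 would take about 33% of control bleeders (about 46 women).
- *Surgeon-decided interruption adds to the problem.* A woman whose compression was interrupted has still received it, so grouping by actual treatment does not obviously move her.

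**Conclusion.** The point holds for the safety population. It rests on a rule that the article states, set against a crossover provision that the article also states, and not on missing detail; an analysis plan that follows the rule as written would inherit the bias. For bleeding-sensitive safety outcomes the direction is against compression, provided rescued women carry more than their proportionate share of the events.

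The size is illustrative only, because the rescue frequency is not given. With no true difference, the as-treated RR is about 1.1 to 1.2 if 10% of control events fall in rescued women, about 1.5 to 1.6 if 25% do, and about 2.7 to 2.9 if 50% do. These figures assume a binary harm, equal arms of 1123, and rescue in 1.24% to 6.2% of controls. For creatinine and eGFR only the direction is argued, and no size was calculated.

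The ITT safety comparison, the primary result and the confirmatory secondary results are not affected, nor is the sample size.

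**What to change.** Before database lock, add to the definitions of the analysis populations:

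1. The comparison by randomised arm (ITT) is the lead safety analysis.
2. In the treatment-received set, control women given compression in response to bleeding are not counted as compression patients. They are shown as a separate descriptive group, with no formal comparison of routine compression against the controls who remain, since Step 4 shows that this is biased as well. A control woman is reclassified only if compression was started at delivery as prophylaxis in error.
3. When the per-protocol set is defined, control women are not excluded because of permitted rescue compression.

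The cost is a few sentences and a slightly more complex safety table. Duration and deviations are already noted. The article does not say that the reason for compression in a control woman is captured, so this should be checked; where the reason is unknown, she can go in the separate group. The clinical rescue rule, the sample size and the confirmatory testing stay as they are.
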